#### Evaluation

At the end of the study, patients will be asked to evaluate their experiences during the study period. In addition, the intervention group will be asked to evaluate their experience of the intervention. The control group will be asked about their need for more psychosocial support during treatment or follow up.

### Data management

We expect most patients will fill out the questionnaires electronically. The results of the questionnaires will be converted to SPSS by a data manager. Only the investigators have access to the coding, storage of all questionnaires and the final dataset. The paper and pencil questionnaires and medical characteristics will be entered in the SPSS database by a research assistant. For the validity of these data, for 10 % of the data double entry of data will be done. A statistician will check data value ranges. All source data will be stored for 15 years.

### Power calculations

Based on prior clinical studies [34] a difference of 10 points in the EORTC QLQ-C30 and its subscales is considered a clinically relevant difference for patients with cancer. The power of the study to detect an effect of 10 points or more is calculated as follows.

The primary outcome is the global quality of life subscale of the EORTC QLQ-C30 (sd = 22.7) at the end of the study [43]. However, we aim for sufficient power for the most important secondary outcomes – the subscales: role function, emotional function, cognitive function and social function of the EORTC QLQ-C30 (clinically relevant difference 10 and sd = 18.7 – 22.8) [43]. Therefore, we are aiming for 84 patients per group. The power of the primary outcome then becomes more than 96 %, and for the relevant subscales at least 80 %, when analyzing these outcomes with adjustment for baseline (i.e., an ANCOVA which has as much power as the *t*-test or more depending on the correlation of the baseline measurement with the measurement at the end of the trial). Taking a drop-out of at most 15 % into account, a total number of 193 patients needs to be included to have sufficient power for the primary and secondary outcomes.

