### Randomization

The expectation is that approximately 75 % of the patients will receive hormonal therapy. Since mood swings and fatigue are known side effects of hormonal therapy [31], we will stratify for hormonal treatment. We therefore will use a randomized block design, prepared by an independent statistician. The patients will be randomized in a 1:1 ratio, immediately after assessment of the adjuvant treatment plan, which includes the use of adjuvant hormonal therapy. Random assignment using sequentially numbering will be done by a physician not involved in the study. The result of the randomization will be communicated by e-mail or mail to the patient by the investigator.

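### The power of more than 96% claimed for the primary outcome does not follow from the stated SD of 22.7, 10-point difference and 84 per group, which give about 81% before baseline adjustment

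*Protocol article*

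**What the plan says.** All the relevant figures stand in the Power calculations section of the protocol article.

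- Effect: "The power of the study to detect an effect of 10 points or more is calculated as follows".
- Primary outcome: "The primary outcome is the global quality of life subscale of the EORTC QLQ-C30 (sd = 22.7) at the end of the study".
- Key secondary outcomes (role, emotional, cognitive and social function): "clinically relevant difference 10 and sd = 18.7 – 22.8".
- Sample size, justified by those secondary outcomes: "Therefore, we are aiming for 84 patients per group".
- Resulting power: "The power of the primary outcome then becomes more than 96 %, and for the relevant subscales at least 80" per cent, for an analysis adjusted for baseline.
- Method: "an ANCOVA which has as much power as the *t*-test or more depending on the correlation of the baseline measurement" with the final one. No value for the correlation is given.

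The section does not state the significance level or whether the test is one- or two-sided. Allocation is equal (Randomization section: "The patients will be randomized in a 1:1 ratio").

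**The concern.** At a fixed difference, sample size and type of test, power depends only on the SD. The primary outcome's SD of 22.7 is all but equal to the largest subscale SD of 22.8, yet one is credited with over 96% power and the other only with a floor of 80%.

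The reasoning behind the sample size fails for the same reason. The text presents the subscales as the outcomes that call for 84 per group, with ample power for the primary outcome as a by-product. An outcome whose SD is near the top of the subscale range cannot have that much to spare.

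This is the headline power of the primary comparison, in a trial meant to inform whether the Distress Thermometer becomes routine care. A reader who accepts the figure will believe that a 10-point benefit would be missed less than 4 times in 100, and may take a null result as firmer evidence against the intervention than the design supports.

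**Working it through.** **Inputs (Power calculations section).** Difference d = 10; n = 84 per group; SD 22.7 (primary), 18.7 to 22.8 (subscales). Assumed: two-sided alpha 0.05.

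**Formula.** Two-sample t-test with noncentrality d / (SD × √(2/n)) on 2n − 2 = 166 degrees of freedom; the critical value is 1.974. For ANCOVA with baseline-to-final correlation r, SD is replaced by SD × √(1 − r²).

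**Step 1: the subscale figure reproduces.** At SD 22.8 the noncentrality is 10 / (22.8 × √(2/84)) = 2.842, and power is 80.7%. This matches the stated floor of 80% with no gain from baseline. At SD 18.7 power is 93.1%.

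**Step 2: the primary figure does not.** At SD 22.7 the noncentrality is 10 / (22.7 × √(2/84)) = 2.855, and power is 81.0% (81.5% by the normal approximation). The type II error is 19%.

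**Step 3: other readings of the inputs, at SD 22.7.**

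| Reading | Power |
|---|---|
| One-sided alpha 0.05 | 88.5% |
| One-sided alpha 0.10 | 94.1% |
| 97 per group (193 randomised, no drop-out) | 86.3% |

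None reaches 96%.

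**Step 4: gain from ANCOVA, two-sided 0.05, 84 per group.**

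| r | SD 22.7 (primary) | SD 22.8 (subscale) |
|---|---|---|
| 0.2 | 82.6% | 82.2% |
| 0.3 | 84.5% | 84.2% |
| 0.4 | 87.2% | 86.9% |
| 0.5 | 90.6% | 90.4% |
| 0.6 | 94.4% | 94.2% |
| 0.65 | 96.2% | 96.1% |

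Power of 96% with 84 per group needs a residual SD of 17.36, so r = √(1 − (17.36/22.7)²) = 0.644. The two columns never differ by more than about 0.3 points, so a common correlation cannot separate the primary outcome from the SD 22.8 subscale.

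**Step 5: what 96% would take without a correlation.** At SD 22.7 and 10 points, 143 per group. With 84 per group, a true difference of about 13.1 points.

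**Step 6: the sample-size reasoning.** For 80% power without adjustment the primary outcome needs 82 per group and the SD 22.8 subscale 83. The subscales therefore add one patient per group. If r = 0.65 had been used throughout, 49 per group would give the SD 22.8 subscale 80%, and the choice of 84 would be unexplained.

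**The case against.** The power sentence is expressly about a baseline-adjusted analysis, and the text says that the gain depends on the correlation. At least 80% is a floor, so it does not formally contradict 96% for another scale, and scales may differ in their baseline correlations. The 19% error is thus the upper end for the planned ANCOVA at SD 22.7; with r between 0.3 and 0.5 it would be about 15% to 9%. The slip may also lie in the SD: an SD of about 17.4 would give 96%, and would fit the statement that the subscales drive the sample size. Finally, a null result will be judged mainly from the estimate and its confidence interval, and the planned sample size does not depend on the 96%.

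Much of this is fair, and it governs how the point should be worded. The 81% is the power before baseline adjustment, and the document cannot show which figure is wrong. What does not stand is the defence of the sentence as printed. The 96% needs a correlation of about 0.64 between a score before treatment and one some two years after adjuvant treatment, which the article neither states nor hints at. The subscale figure is matched with no correlation at all. A high correlation reserved for the primary outcome alone would need its own justification.

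**Conclusion.** The concern holds. On the stated SD, difference and group size, power for the primary outcome is about 81% before baseline adjustment, some 15 percentage points below the stated figure. It stays below 96% for any baseline correlation under about 0.64. One of three things must be true: the power is wrong, the SD of 22.7 is wrong, or a decisive assumption was left out. Each calls for a correction.

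The 81% rests on an assumed two-sided alpha of 0.05; one-sided testing at 0.05 or 0.10 does not rescue the claim. The practical damage is limited. With 84 evaluable patients per group the primary comparison still exceeds 80% power, so the design does not fail on this ground; what is lost is the margin that the article claims.

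**What to change.** Replace the power statement for the primary outcome with, for example: with 84 evaluable patients per group, two-sided alpha 0.05, an SD of 22.7 and a difference of 10 points, power is about 81% before adjustment for baseline.

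If a baseline correlation was used, state its value and source, and recalculate the primary outcome and all the subscales with it. If 22.7 is not the SD of the global scale in the cited source, correct the SD and show the power that follows. In every case state the alpha and sidedness, and revise the sentence that attributes the sample size to the subscales so that it agrees with the corrected figures.

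The cost is one or two sentences and a less favourable stated power. The analysis and the target of 84 evaluable per group are unchanged. That last point depends on 84 per group actually being evaluable: the article says "Taking a drop-out of at most 15 % into account, a total number of 193 patients needs to be included", and 193 × 0.85 = 164, or 82 per group, which gives 80.1% at SD 22.7 and 79.7% at SD 22.8 before adjustment. The recruitment total should be checked when the paragraph is corrected.

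### A total of 193 keeps 84 patients per group only up to about 13% drop-out, not the 15% stated

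*Protocol article*

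**What the plan says.** The Power calculations section of the protocol article takes 10 points as the clinically relevant difference. It gives an SD of 22.7 for the primary outcome and a range for the main secondary subscales ("clinically relevant difference 10 and sd = 18.7 – 22.8"). From these it sets the target: "Therefore, we are aiming for 84 patients per group". The Randomization section fixes equal allocation ("The patients will be randomized in a 1:1 ratio"), so the target is 168 patients in total.

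The drop-out allowance follows: "Taking a drop-out of at most 15 % into account, a total number of 193 patients needs to be included". The section presents this total as sufficient for both the primary and the secondary outcomes. It states a power of at least 80% for the relevant subscales, and it states this for an ANCOVA adjusted for baseline. It does not write out how 193 was obtained, and it gives no alpha, sidedness or baseline correlation.

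**The concern.** A drop-out rate normally refers to the patients enrolled. To keep a required number after losing a fraction d of those enrolled, the required number is divided by (1 − d). Multiplying it by (1 + d) adds a fraction of the completers instead, and always falls short. The stated total agrees with the multiplication and not with the division.

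At stake is whether the published sample size follows from its own inputs. A reader who takes the section at its word will believe that 84 per group remain at the stated drop-out limit. The target of 84 also sits close to the number that the widest subscale needs for 80% power without baseline adjustment, so it is fair to ask what a small shortfall does.

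**Working it through.** **Inputs.** From Power calculations: 84 per group, drop-out of at most 15%, total of 193, difference of 10 points, SD 22.7 (primary) and 18.7 to 22.8 (subscales). From Randomization: 1:1 allocation. Assumed, because the article does not state it: two-sided alpha of 0.05. The drop-out arithmetic does not depend on that assumption; only the power figures do.

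**Step 1. Reproduce the stated total.**
- Required after drop-out: 2 × 84 = 168.
- Multiplication: 168 × (1 + 0.15) = 193.2, which rounds to the stated 193.

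**Step 2. The total that 15% of those enrolled implies.**
- 168 / (1 − 0.15) = 168 / 0.85 = 197.6, rounded up to 198 (99 per group).
- Difference: 198 − 193 = 5 patients, and 5/198 = 2.5%.

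**Step 3. What 193 delivers.**
- At 15% loss: 193 × 0.85 = 164.05, so about 164 patients or 82 per group.
- Loss at which 168 still remain: 1 − 168/193 = 0.1295, that is 12.95%.
- The allowance of 193 − 168 = 25 patients is 14.9% of 168 but 12.95% of 193.

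**Step 4. Effect on power, without baseline adjustment.** Two-sample t-test, noncentrality = 10 / (SD × √(2/n)), 2n − 2 degrees of freedom. For SD 22.8 the noncentrality is 10 / (22.8 × √(2/84)) = 2.84 at 84 per group and 10 / (22.8 × √(2/82)) = 2.81 at 82.

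| SD | 84 per group | 82 per group |
|---|---|---|
| 22.8 (widest subscale) | 80.7% | 79.7% |
| 22.7 (primary outcome) | 81.0% | 80.1% |
| 18.7 (narrowest subscale) | 93.1% | 92.6% |

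The normal approximation gives 81.1% and 80.2% for SD 22.8, so on that formula even the widest subscale stays above 80%.

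**Step 5. Effect on power, with baseline adjustment.** With baseline correlation r, the residual SD is SD × √(1 − r²). At 82 per group and SD 22.8, a correlation of about 0.084 brings the t-test figure back to 80%. Correlations of 0.2, 0.3 and 0.5 give 81.3%, 83.3% and 89.7%.

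**The case against.** A reader might infer that, at 15% drop-out, the stated subscale power of at least 80% fails and the trial is underpowered. The document does not support this. The 79.7% belongs to an unadjusted t-test at the single widest SD, whereas the section states its power for a baseline-adjusted ANCOVA. The shortfall of 0.3 points disappears with a correlation of about 0.084, and it does not appear at all under the normal approximation. At SD 22.7 and 18.7, power stays above 80% even without adjustment.

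The Statistical analysis section also plans last observation carried forward for the ANCOVA. Patients who leave after giving earlier measurements could therefore still be analysed, and the analysed number could exceed 164. This stands only in part: the power section itself inflates for drop-out in order to protect 84 per group, and a carried-forward value is not equivalent to an observed one.

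It can also be said that the multiplication by 1.15 is not documented. That is correct. The match makes it the likely route, but the point does not need it, since 193 falls short of the target at 15% loss whatever formula was used.

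Finally, the 15% might have been meant as a share of 168. That would explain the figure, but it is not the ordinary reading of a drop-out rate, and the tolerable loss among those enrolled would still be about 13%.

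None of this reconciles 84 per group, 15% and 193.

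**Conclusion.** The point holds, as a minor error in a stated figure. With drop-out read as a share of those enrolled, 84 per group, 15% drop-out and a total of 193 cannot all be true. A total of 193 tolerates about 13%, and 15% leaves about 82 per group or calls for 198.

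The consequence is small: two patients per group at the end of the trial, and about one percentage point of unadjusted power at SD 22.8 under the assumed two-sided alpha of 0.05. It changes no design choice and no analysis, and it gives no ground for saying that the subscale power claim fails.

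One neighbouring figure should be kept apart. The section states a power above 96% for the primary outcome at 84 per group. The inputs given yield about 81% without adjustment, and 96% would need a baseline correlation near 0.64, which is not stated. The drop-out arithmetic does not explain that gap.

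**What to change.** Reword the sentence that gives the total, in one of two ways:
- say that 193 patients allow for a drop-out of about 13% while keeping 84 per group; or
- keep the 15% and say that it would leave about 82 per group, noting that 198 is the total that 15% implies for 84 per group.

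Say in either case that the percentage refers to patients enrolled. Do not add a power figure for the primary outcome to this sentence unless the stated value above 96% is reconciled separately; otherwise the paragraph would contain a new contradiction. The cost is one sentence, with no additional patients and no change to the analysis.

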### Statistical analysis

The primary analysis is the comparison of the primary outcome global quality of life subscale of the EORTC QLQ-C30 as measured at the end of the research period analyzed by ANCOVA, i.e., an adjustment for baseline will be included. The secondary analysis of the primary outcome is a repeated measurements analysis of the sequence of the repeated measurements in order to compare the trends between the two groups (mixed model for repeated measurements). Similar analysis will be carried out on the secondary outcomes. Subgroup analysis will be performed on demographic and treatment characteristics.

Missing data will be analyzed with the last observation carried forward method for the ANCOVA and a sensitivity analysis assuming missing data to be missing-at-random will be performed using a mixed model for repeated measurements. Patients who have died, had recurrence or metastasis of the breast cancer, or were diagnosed with another malignancy during the study will be considered to have dropped out of the study from that event onwards.

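### Randomisation is stratified by planned hormonal therapy, but no stated model contains the stratum; the reported standard error is then slightly too large (low severity, free improvement)

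*Protocol article*

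**What the plan says.** The Randomization section of the protocol article describes a randomised block design with 1:1 allocation and gives a prognostic reason for the stratification: "Since mood swings and fatigue are known side effects of hormonal therapy [31], we will stratify for hormonal treatment". It also gives the expected stratum size: "The expectation is that approximately 75 % of the patients will receive hormonal therapy". Allocation follows the adjuvant treatment plan, so the stratum is the planned use of hormonal therapy and is known at randomisation.

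The Statistical analysis section defines the primary analysis of global quality of life at the end of the study as "analyzed by ANCOVA, i.e., an adjustment for baseline will be included". The Power calculations section describes the same ANCOVA, again by its baseline adjustment alone. For the mixed model for repeated measurements no covariates are listed. Secondary outcomes are to be analysed in a similar way. The only other use of treatment characteristics is in subgroup analyses, which do not adjust the main comparison.

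**The concern.** A factor that is thought prognostic enough to stratify on normally belongs in the model. Stratified blocks make the arms nearly equal on hormonal therapy, so that factor contributes almost nothing to the sampling variation of the treatment difference. A model without the factor still counts the between-stratum variance as residual noise. Its standard error is therefore larger than the true sampling variation of the estimate.

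The baseline covariate is unlikely to make up for this. The baseline questionnaire is preferably completed before surgery or neo-adjuvant chemotherapy, so it cannot carry an effect of hormonal therapy that starts later. Hormonal therapy may also continue into follow-up, because it is excepted when the article defines the completion of adjuvant treatment.

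What is at stake is how accurately the standard error, confidence interval and p-value of the primary comparison are reported. The same holds for the role, emotional, cognitive and social function subscales, for which the trial was also sized.

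**Working it through.** The plan states no figure for the effect of the stratum, so there is none to reproduce. The check asks how far the reported standard error departs from the true one.

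**Inputs from the article**
- Proportion on hormonal therapy: p = 0.75 (Randomization).
- SD of the primary outcome: 22.7, so the total variance is 22.7² = 515.29 (Power calculations).
- 84 evaluable patients per group, 168 in all, and a relevant difference of 10 points (Power calculations).

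**Assumptions, not given in the article**
- Stratum difference d in the final score: 5, 10 or 15 points.
- Baseline correlation ρ: 0 or 0.5.
- Two-sided 5% test.
- Baseline score independent of the stratum.

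**Formulas**
- Between-stratum variance: p(1 − p)d² = 0.1875 d².
- Residual variance of the ANCOVA without the stratum: 515.29 × (1 − ρ²), which is 515.29 at ρ = 0 and 386.47 at ρ = 0.5.
- Share of residual variance due to the stratum: s = 0.1875 d² / residual variance.
- Ratio of reported to true standard error: k = 1/√(1 − s).
- True type I error: 2 × (1 − Φ(1.96 k)).

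**Example, d = 10**
- Between-stratum variance: 0.1875 × 100 = 18.75.
- ρ = 0: s = 18.75/515.29 = 3.6%; k = 1/√0.9636 = 1.019; type I error 4.6%.
- ρ = 0.5: s = 18.75/386.47 = 4.9%; k = 1/√0.9515 = 1.025; type I error about 4.5%.

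| d (points) | ρ | Share s | SE too large by | Type I error |
|---|---|---|---|---|
| 5 | 0 | 0.9% | 0.5% | 4.9% |
| 10 | 0 | 3.6% | 1.9% | 4.6% |
| 15 | 0 | 8.2% | 4.4% | 4.1% |
| 5 | 0.5 | 1.2% | 0.6% | 4.9% |
| 10 | 0.5 | 4.9% | 2.5% | 4.5% |
| 15 | 0.5 | 10.9% | 5.9% | 3.8% |

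**Simulation check.** Each scenario used 6,000 trials of 168 patients, with assumed blocks of four within stratum, 75% prevalence and total SD 22.7. The ANCOVA was fitted with baseline only and with baseline plus stratum. Power is for a true difference of 10 points.

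| d | ρ | Type I error, baseline only / plus stratum | Power, baseline only / plus stratum |
|---|---|---|---|
| 0 | 0 | 4.7% / 4.7% | 80.1% / 80.2% |
| 5 | 0 | 5.1% / 5.2% | 80.5% / 80.7% |
| 10 | 0 | 4.7% / 5.1% | 80.7% / 81.6% |
| 15 | 0 | 4.0% / 4.9% | 81.1% / 83.6% |
| 0 | 0.5 | 4.7% / 4.6% | 90.8% / 90.8% |
| 5 | 0.5 | 4.8% / 5.1% | 90.5% / 90.7% |
| 10 | 0.5 | 4.4% / 5.0% | 91.0% / 91.6% |
| 15 | 0.5 | 3.4% / 4.4% | 92.1% / 93.8% |

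The Monte Carlo standard error of a 5% rate is √(0.05 × 0.95/6000) = 0.28 percentage points, so small differences from the formula are noise.

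At d = 10 and ρ = 0.5, the mean reported standard error is 3.04 without the stratum and 2.97 with it. The actual sampling SD of the estimate is 2.96 under both models. The estimate is therefore equally precise either way, and only the baseline-only standard error overstates its uncertainty.

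**The case against.** The strongest objection is that this argues from silence in a condensed article. The phrase about baseline can be read as explaining why the analysis is an ANCOVA and not a t-test. The article never says that baseline is the sole covariate, and for the mixed model it lists none. A full protocol or analysis plan, not shown here, could contain the stratum. This stands as a limit on confidence. It does not remove the point: the article describes the primary ANCOVA twice, each time by baseline adjustment alone, although it gives a prognostic reason for its stratification.

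A second objection is that the effect is small. This also stands. The article gives no effect of hormonal therapy on global quality of life, only the mention of mood and fatigue. Differences of 10 or 15 points equal or exceed what the article itself calls clinically relevant. At 5 points the consequence is negligible.

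Three stronger readings are tempting, and the documents do not support them:
- **The benefit of stratifying is lost.** Balance between arms is kept, and the sampling SD of the estimate is the same under both models. Only the reported standard error misses the gain. The article also never says that a smaller standard error was the aim.
- **The result could be biased or falsely positive.** The error goes the other way: the type I error lies at or below its nominal level.
- **The trial has about 81% power and cannot afford any loss.** That figure (84 per group, difference 10, SD 22.7, two-sided 5%) holds only at zero baseline correlation. At 0.5 it is about 91%, and the article itself says that the ANCOVA may do better than the t-test. Whether the stated power of more than 96% can be reproduced is a separate question.

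**Conclusion.** The point holds as a low-severity, free improvement. The trial stratifies on a factor that it expects to matter, and it names baseline as the only adjustment in its primary model. If the factor affects the outcome, reported intervals are slightly too wide and p-values slightly too large. Over the assumed range of 5 to 15 points and baseline correlations of 0 and 0.5, the standard error is about 0.5% to 5.9% too large, the true type I error is about 4.9% down to 3.8%, and the power lost is about 0 to 2.5 percentage points. If hormonal therapy has no effect on the outcome, nothing is lost. The direction is certain whenever there is an effect. The size is not, because it rests on a stratum effect and a baseline correlation that the article does not give.

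**What to change.** Name the randomisation stratum (planned hormonal therapy, yes or no, as randomised and not as received) as a fixed covariate next to baseline in the primary ANCOVA. Do the same in the mixed model for repeated measurements and in the corresponding models for the secondary outcomes. If a full protocol or analysis plan already includes the term, it is enough to say so.

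The cost is one degree of freedom and no new data, since the stratum is recorded at randomisation. The term should be fixed before the outcome data are examined: in a non-blinded trial, a covariate added afterwards could look chosen for its result.
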